### 4.1.5 Replacing Ineligible Camps

Following random selection, camp rosters will be collected from leaders of all selected camps. Selected camps will be replaced if current rosters do not meet size eligibility requirements reported during camp verification, or camps refuse to participate. To replace ineligible or non-interested camps, another random selection using probability proportionate to size will be conducted from all eligible camp groups. The group selected in the same numeric order as the group with the camp to be replaced (e.g. 15^th^ group selected) will have a camp selected in to the study through simple random selection within the group. This process will be repeated until the sample contains 60 eligible and consenting camps.

## 4.2 Camp Treatment Assignment Procedures

Following random selection, camps will be randomly assigned to a condition 1 or 2, not yet linked to intervention or control. Following up on the grouping procedure used during random selection to minimize potential contamination, groups with single camps selected in the study will first be randomly assigned to condition 1 or 2. Groups with two camps selected in to the study will next be randomly assigned to condition 1 or 2, followed by groups with three camps.

Treatment assignment for the 60 randomly selected and eligible camps will be conducted during a CAB meeting. At the meeting an individual representing condition 1 or 2 will be presented with 5 balloons, each with a folded paper enclosed. In three of the balloons the paper will read “Try again,” one paper will contain the number 1 and one paper will contain the number 2. The individual will be asked to pop one balloon and read the enclosed paper. A “try again” message will prompt the individual to select and pop another balloon. The first number encountered upon popping will represent the group to receive the intervention condition. For example, if the number 2 was encountered first, all camps in Condition 2 are assigned to the intervention condition.

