### 3.2.3 Second Primary Aim

To achieve our second primary aim, to evaluate the efficacy of a combined microfinance and health leadership intervention we will conduct a trial among 1252 men in 60 camps that are randomly selected proportionally across four wards. Our primary hypothesis is that the combined microfinance and health leadership intervention will be associated with a lower incidence of sexually transmitted infections and other HIV risk behaviors and less perpetration of violence against female sexual partners over time among men in camps randomized to the intervention as compared to men in camps randomized to the control condition. We also hypothesize that men’s hope for, and orientation towards, the future, as well as the support, social influence and the collective efficacy of their networks, will mediate the effect of the intervention on these outcomes.

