# 4. STUDY ENROLLMENT

This study will take place in Kinondoni district, the most populous (over 1 million) and most impoverished of the three districts in Dar es Salaam, Tanzania.([Statistics, 2002](#_ENREF_90)) Four wards in Kinondoni characterized by high risk for HIV among young people have been selected for recruitment. These four wards include Manzese (population 66,543), Tandale (population 44,853), Mwananyamala (population 44,344), and Mabibo (population 77,639). In all four wards over a third of the population are males aged 15-29 (range among four wards is 36-38%).([Statistics, 2002](#_ENREF_90)) Illicit drug use, alcohol use, and commercial sex are common to the four wards. In one study of HIV infection among drug users, 66.7% of syringes from male injectors in Manzese and Tandale tested HIV positive and 40% of syringes from male injectors in Mwananyamala tested HIV positive.([McCurdy, Ross, Kilonzo, Leshabari, & Williams, 2006](#_ENREF_55)) Social venues called camps, where young men socialize, have been identified as locations of focus for this study.

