### 4.1.4 Camp Random Selection

60 camps will be randomly selected in to the study, and later assigned in to one of two conditions – intervention or control. Due to the density of camps within wards and the contiguous nature of some camps, measures will be taken to minimize contamination of potential intervention and control camps before random assignment. The following steps will be taken during the random selection of camps.

1. Local staff will group geographically contiguous camps posing a threat to potential contamination. Eligible camps will be mapped by GPS coordinates on a street layout of the four wards to facilitate grouping. Groups will contain up to 6 camps, individual isolated camps will not need to be put in a group.
2. Groups will be selected for inclusion in the study using probability proportionate to size. Thus, groups with numerous camps of large membership have the potential to be selected more than once.
3. Simple random selection of camp(s) will be completed among camps in each group selected in to the study. Camps from the same group randomly selected in to the study will necessarily receive the same condition during the condition assignment phase.

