## 6.3 Baseline Behavioral Survey

Eligible and consenting camp members in the 60 selected camps will participate in a survey assessing socio-demographics, outcome variables and mediating variables (Appendix D). The questionnaires will be administered using CAPI by trained interviewers who are not intervention facilitators. The interview will last approximately 60 minutes. Interviews will take place in a central location within each ward, interviewers split between the four wards. Participants who appear influenced by drugs will be asked to return for an interview the next day.

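### Camp selection, replacement and assignment use no ward stratum, so the ward proportionality stated in 3.2.3 holds only in expectation and chance ward imbalance between arms is likely, at some cost in precision

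*Protocol*

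**What the plan says.** The protocol describes how camps enter the trial and reach an arm in five places.

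- **3.2.3** refers to "60 camps that are randomly selected proportionally across four wards".
- **4.1.4** has staff form groups of up to six contiguous camps on a map of the four wards. Then: "Groups will be selected for inclusion in the study using probability proportionate to size". No ward stratum is named. It adds: "Camps from the same group randomly selected in to the study will necessarily receive the same condition".
- **4.1.5** handles camps that refuse or turn out to be the wrong size: "another random selection using probability proportionate to size will be conducted from all eligible camp groups". The replacement need not come from the ward of the lost camp.
- **4.2** orders assignment by the number of selected camps per group: "groups with single camps selected in the study will first be randomly assigned to condition 1 or 2", then groups with two, then groups with three. Ward plays no part. The balloon draw only decides which condition number becomes the intervention.
- **9.1.3** describes a simple random sample of camps with equal-probability randomisation.

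On fieldwork, 6.3 states: "Interviews will take place in a central location within each ward, interviewers split between the four wards". On adjustment, 3.3 says non-equivalence at baseline will be controlled for at endline, and 9.1.3 allows covariates where necessary. Neither names ward.

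**The concern.** Section 3.2.3 states a property of the sample that the written steps do not secure, and the descriptions of the draw in 3.2.3, 4.1.4 and 9.1.3 differ. Ward is the protocol's own geographic unit, and two features give it a possible link to outcome. First, interviewers are divided by ward, so ward differences in self-reported violence can include interviewer differences. Second, section 4 gives one ward contrast in an HIV marker: "66.7% of syringes from male injectors in Manzese and Tandale tested HIV positive", against 40% in Mwananyamala.

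Whole groups go to one arm, so fewer than 60 independent units may be randomised, and uneven ward splits become more likely. Any between-ward variance then stays in the error of the arm comparison. A visibly lopsided ward-by-arm table would also invite argument about adjustment chosen after the fact.

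**Working it through.** **1. The plan's own figures (9.1.1).** Sample size: 54 × 36.2 = 1,954.8 and 54 × 52 = 2,808, as stated. Design effect 1 + (m − 1) × ICC, with m = 52 × 0.8 = 41.6 after 20% attrition: 1 + 40.6 × 0.01 = 1.41 and 1 + 40.6 × 0.032 = 2.30. Both ends of the stated 1.4 to 2.3 reproduce.

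**2. Ward shares.** The number of camps per ward is not given, so the section 4 populations serve as a proxy (assumption). The total is 66,543 + 44,853 + 44,344 + 77,639 = 233,379. Shares are 28.5, 19.2, 19.0 and 33.3%, which give proportional targets of 17.1, 11.5, 11.4 and 20.0 camps out of 60.

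**3. Selection without a ward stratum.** If each draw brings in one camp, the count per ward is multinomial, with SD about 3.0-3.6 camps. The 95% ranges are 10-24, 6-18, 6-18 and 13-27. With 34 single camps, 10 pairs and 2 triples (46 units), the largest ward receives 11-29 camps against a target of 20.

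**4. Assignment without a ward stratum.** Wards are drawn by the shares above, and each group-size class is halved at random. The group structures are assumed.

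| Structure (singles / pairs / triples) | Units | Chance that some ward with ≥5 camps splits 65:35 or worse |
|---|---|---|
| 60 / 0 / 0 | 60 | 56-57% |
| 34 / 10 / 2 | 46 | 72-73% |
| 24 / 12 / 4 | 40 | 77% |

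The SD of the arm difference in one ward's share of camps is 10-16 percentage points. A second criterion, with ward counts fixed at 17/12/11/20, points the same way. The chance that some ward's arms differ by 6 or more camps is 31% with all single camps, 50% with 46 units and 69% with 32 units.

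**5. What removing ward variance would gain.** If ward accounts for a fraction f of the camp ICC, the variance ratio is [1 + (m − 1) × ICC × (1 − f)] / [1 + (m − 1) × ICC]. Here m = 1,249 / 60 = 20.8, using the Protocol Summary's study size.

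| ICC | f | Ratio | Variance cut | 80% power becomes |
|---|---|---|---|---|
| 0.01 | 0.25 | 1.149 / 1.198 | 4% | 82% |
| 0.01 | 0.50 | 1.099 / 1.198 | 8% | 83% |
| 0.032 | 0.25 | 1.475 / 1.634 | 10% | 84% |
| 0.032 | 0.50 | 1.317 / 1.634 | 19% | 88% |

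At f = 0 or ICC = 0 the gain is nil.

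**6. If ward variance comes on top of the planned ICC.** Section 1.7 places the earlier camp survey in one ward. If the 9.1.1 ICCs come from it, they contain no between-ward variance. Take a 41% violence rate (the lifetime figure in 1.7, used as an assumption), OR 0.65 and 2,808 × 0.8 / 2 / 2.3 = 488 effective men per arm: power is 89.7%. Suppose Manzese and Tandale (47.7% of the population) run 5 points higher. The added ICC is 0.05² × 0.477 × 0.523 / (0.41 × 0.59) = 0.0026, the design effect rises to 2.40 and power falls to 88.4%. At 10 points the added ICC is 0.0103, the design effect 2.72 and power 84.2%. Under the same assumptions, ward imbalance adds an SD of 0.7-1.0 points (5-point gap) or 1.3-2.0 points (10-point gap) to the arm difference.

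**The case against.** Unstratified cluster randomisation is a legitimate design. Chance ward imbalance is part of the between-cluster variance that a correct cluster-level interval covers. Selection with probability proportionate to size gives proportional ward shares in expectation, and 4.1.4 is silent on ward rather than ruling it out, so 3.2.3 is not guaranteed rather than flatly contradicted. All of this stands.

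A reader might infer that ward confounds the arm effect on both primary endpoints. The documents do not support that. Imbalance under valid randomisation is not systematic bias. Interviewer differences can affect self-reported violence but cannot reach a urine PCR result. The syringe contrast concerns male injectors in three wards, with Manzese and Tandale pooled and no figure for Mabibo; it is not STI or violence in camp men. Section 4 also describes drug use, alcohol use and commercial sex as common to all four wards. No ward-level rate is given for either primary endpoint.

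The size of the gain also rests on assumptions. The group structures and the ward share of the ICC are not in the protocol, and both stated ICC ranges start at 0.00. The 65:35 criterion is met if any one ward reaches it, and an 8:4 split of 12 camps is enough.

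The adjustment wording in 3.3 and 9.1.3 is a partial safeguard, and violence is measured at baseline in all participants. But that wording leaves the use of ward to a later decision. The model term could sit in an SAP that is not shown, so its absence is not the finding. Selection, replacement and assignment are protocol steps, written out here, and they do not deliver what 3.2.3 states.

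**Conclusion.** The point holds as one of consistency and precision. Section 3.2.3 states ward proportionality; 4.1.4, 4.1.5 and 4.2 do not secure it; 9.1.3 describes yet another draw. Given population-based ward shares and 40-60 randomised units, a 65:35 or worse split in at least one ward is more likely than not (56-77%).

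The consequence depends on between-ward variance, which the protocol does not give. It is nil if wards do not differ. If ward explains 25-50% of the ICC, removing it cuts variance by about 4-8% at ICC 0.01 and 10-19% at ICC 0.032. Violence is the endpoint where an effect is most plausible; an effect on STI is possible but not shown. The validity of the randomisation is not in question. The change is worth making because it costs little.

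**What to change.** - **3.2.3, 4.1.4, 4.1.5 and 9.1.3:** describe one and the same draw.
- **4.1.4 and 4.1.5:** fix the number of camps per ward in proportion, draw groups within ward, and take each replacement from the ward of the lost camp. Allocate any group that crosses a ward boundary to one ward beforehand.
- **4.2:** balance assignment across wards as far as group sizes and the 30:30 split allow.
- **9.1.3:** prespecify ward as a fixed effect in the 12- and 30-month models, and report the ward-by-arm table. This step still works if assignment is already done.

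The cost is a rewrite of the draw and assignment steps and 3 degrees of freedom out of about 40-60 units, with no new data. The downside is a more constrained draw: four wards by three group-size classes make up to 12 cells, some with very few groups, so exact balance in each will not be possible.

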## 4.3 Participant Screening and Enrollment

All members of camps selected in to the trial are preliminarily eligible for inclusion in the study. Following random selection, camp leaders from camps selected in to the trial will be given a camp roster template to complete. The camp leader will be responsible for recording the name of every camp member as well as birthdate, gender, phone numbers, length of time as camp member, whether or not the member intends to stay in the city for the next 30 months, and contact numbers for 2 friends or family members. Participants not meeting eligibility criteria listed below will not be entered in to the study.

### 4.3.1 Participant Eligibility Criteria

Study participants will be male members of camps in Dar es Salaam, Tanzania. Camps are predominately male social groups where members meet in fixed locations. Eligibility criteria for camp members to be able to participate in the study include:

- Participant is at least 15 years old
- Has been member of camp for at least 3 months
- Visits camp at least once a week
- Intends to live in Dar es Salaam for next 30 months
- Willing to give contact information of self and relative or friend

### 4.3.2 Participant Exclusion Criteria

Individuals will be excluded from the baseline behavioral assessment if they meet any of the following criteria:

- Does not meet all inclusion criteria
- Unable to participate due to psychological disturbance, cognitive impairment or threatening behavior

## 4.4 Participant Retention

At enrollment into this study, staff will record locator information (name, telephone number, typical place of residence or sleeping location) and names of contacts who usually know where to find the participant, with an assurance not to reveal the participant’s involvement in the study.

The following systems are in place at the site for cohort retention:

- **Participant scheduling:** All scheduled appointments and missed appointments will be tracked on both physical contact forms as well as entered in to Computer-Assisted Personal Interviewing (CAPI) tablets.
- **Participant Follow-up:** Study participants who miss scheduled appointments will be contacted within 24 hours by telephone or by home visit if they did not leave a telephone contact.
  - If unsuccessful in contacting participants, we will follow up with contacts they provided of friends or relatives. If participants are not able or do not wish to attend a study visit, reasons for non-attendance will be recorded. Participants are considered lost to follow-up if unable to be contacted through 5 attempts.
    - **Travel Expense Compensation:** Participants will receive monetary compensation of TSH 10,000 for travel expenses to the site where interviews take place.
- **Camp Roster Updates:** After each wave of data collection participant contact information will be updated on physical files.
- **Community Engagement:** Community engagement through CAB meetings will facilitate community support needed to track and follow up with participants. CAB meetings will occur two times per year through the life of the study.
- **Interpersonal Relationship Building:** Appealing to participants interpersonally has been an effective strategy to retain participants. Our staff will have the opportunity to interact with participants during each wave of data collection, and meetings with the CAB and camp leaders.
- **Intervention Activities:** Intervention activities including microfinance repayment and camp health leader conversation documentation offer opportunities to check-in with members about the state of their camp and membership.

## 4.5 Participant Withdrawal

Participants may voluntarily withdraw from the study at any time. If a participant chooses to withdraw during an assessment period they can choose not to have their assessment responses submitted to the study team.

Participants also may be withdrawn if the principal investigator, study sponsor, government or regulatory authorities, or site institutional review boards (IRBs) terminate the study prior to its planned end date. In such cases the Principal Investigator will review the reasons for withdrawal with the IRB and Protocol Biostatistician prior to participant notification. The Principal Investigator may decide to include data collected prior to participant withdrawal in study analyses.

Every reasonable effort will be made to complete a final assessment of participants who leave the study prior to the planned termination date. Study staff will record the reason(s) for all withdrawals from the study in participants’ study records.

# 5. INTERVENTION COMPONENTS

## 5.1 Overview

This study employs a combined microfinance and health leadership behavioral intervention. Prior research has demonstrated that microfinance combined with health interventions reduces poverty and can lead to significant improvement in health outcomes, however these interventions have not been evaluated among young men. The microfinance component provides small loans and business skills training for participants to begin building viable businesses, encouraging increased income. The health leadership component uses nomination of public opinion leaders in camps and health leadership training to inform and encourage leaders to talk with others about HIV risk behaviors and GBV.

## 5.2 Microfinance Implementation

Youth Self-Employment Foundation (YOSEFO), a microfinance institution in Dar es Salaam, will implement the microfinance component of the intervention (www.yosefo.org). YOSEFO has been providing loans to young men and women in Tanzania since1996, and partnered with our team for a pilot of this trial. As of 2011, the total number of YOSEFO clients was 18,200, with an outstanding loan amount of 3.9 billion Tanzanian Shillings ($2.3million USD). The standard principles and practices in microfinance that successfully guided our pilot study and will guide implementation of this study include:

### 5.2.1 Business skill training

Camp members will receive one week training on entrepreneurship skills and loan financing facilitated by YOSEFO. The trainings will focus on how to generate viable business ideas, how to assess markets, how to start and scale up businesses, how to manage businesses, and loan term and repayment (Appendix A).

**5.2.1.1 Entrepreneurship**

Entrepreneurship training will take place during the first four days of the one week training. Lessons will include: Business environment; entrepreneurship and the entrepreneur; marketing, sales and customer service; techniques for business growth and expansion; costs, sales and prices in business; and effects of HIV/AIDS, business and family.

**5.2.1.2 Loan Financing**

Participants will learn the logistics of loan financing during the last day of training. Lessons will include: Obtaining business capital; loan collateral; loan criteria; loans and interest rates; loan groups and centers; loan application; loan repayment.

### 5.2.2 Loan Centers and Groups

To encourage accountability in loan repayment, camp members must form groups of 5 members to receive a loan. All groups in the same camp will form a center for the purpose of repayment. Each center meets weekly at a recurring time for repayment. Repayment of a loan is the responsibility of the borrower, but members are encouraged to follow up on repayment among all group members.

**5.2.2.1 Loan Group Formation**

Camp members will be responsible for forming their own group of five members. Groups are formed during the final day of training with one member being nominated as the group leader.

**5.2.2.2 Center Leadership**

Each center will nominate a chairman, secretary, and discipline master by vote. The chairman will be responsible for collection of weekly installments to present to a Loan Officer. The secretary is responsible for monitoring attendance at repayment sessions. The discipline master enforces any rules created by the center.

### 5.2.3 Loan Financing

All loans are subject to an interest rate and other fees. Participants have a choice of interest paid over a 6 month repayment period (18%) or 9 months (27%). Other fees and deposits include:

- Entry fee (One-time payment of TSH 3,000)
- Loan fee (1% of loan amount)
- Loan insurance (1.5% of loan amount)
- Life insurance (Annual payment of TSH 550)
- Savings (Weekly TSH 2,000 deposit)

(Appendix B)

### 5.2.4 Loan Application

Loan application occurs over three weeks and includes registration, application, and savings deposits of U.S. $5. This process is enacted to establish the habit of participants attending weekly meetings, and to minimize chances of participants borrowing from another institution to fund the savings required to receive a YOSEFO loan. In the first week individuals must register for loans. In the second week individuals complete a loan application form that includes details on the planned business, physical collateral, and contacts for group members. Through these two weeks and the following week leading up to loan disbursal, camp members must deposit the equivalent of 5% of the loan amount to savings before receiving the loan.

